## Discontinuation of treatment

- The patient decides to withdraw from the study.
- Presence of serious adverse events related to the study medication.
- Questionable compliance of the patient.
- Intake of systemic corticosteroids for more than two weeks.
- The patient develops a severe and unstable disease (see also exclusion criteria).
- The diagnosis of Alzheimer’s disease is no longer plausible considering the course of the disease.
- Breaking of the medication code.

## Patient recruitment

Patients will be recruited from the following populations:

- patients referred to the general outpatient clinic and the memory clinic of the Department of Geriatric Medicine, Radboud University Medical Centre Nijmegen
- patients referred to the outpatient clinic of the Department of Neurology, Radboud University Medical Centre Nijmegen
- patients referred to the memory clinic of the Department of Geriatric Medicine, Rijnstate Hospital, Arnhem

Recruitment through public media (e.g. local newspapers) will also be considered.

## Eligibility screening

Screening will be conducted at least 14 days before the patient begins taking study medication. Patients must satisfy the DSM-IV criteria for dementia of the Alzheimer type. Patients must also satisfy the NINCDS-ADRDA criteria for probable Alzheimer’s disease, have a MMSE score between 10 and 26 (both inclusive) and have a responsible caregiver to ensure compliance with the protocol.

To be eligible for the study, patients must satisfy selection criteria. Potentially eligible patients whose screening examinations show any disqualifying abnormality may have their examination to be repeated. Results must be within normal limits or judged not clinically significant before the patient starts treatment with the study medication.

Patients will undergo the following screening assessments (Appendix II): medical history, prior and concomitant medications or therapies, physical examination, vital signs, laboratory evaluations (including Apo E genotyping) and MMSE. Evaluation of the urine, electrocardiogram and CT scan of the brain will be conducted when not performed recently (CT scan > 2 years).

## Information to the family physician

When a patient is enrolled in the clinical trial, his family physician will be informed. The letter contains information about the purpose of the clinical trial, possible adverse events due to the study medication and telephone numbers to contact in case of emergency (Appendix I).

# Duration

## Patients

The study duration for the patient, from baseline to final evaluation, is one year. Six visits will take place in which different evaluations will be conducted. The evaluation schedule is specified in Appendix II.

## Study

The study duration, from recruitment of patients to the final analysis and reporting of results, will be four years. The following breakdown of this period should be considered:

- year 1: recruitment of 55 patients
- year 2: recruitment of 55 patients
- year 3: recruitment of 50 patients
- year 4: analysis and reporting of results

# Ethics and good clinical practice

## Declaration of Helsinki

The study will be conducted in accordance with the “Declaration of Helsinki”, concerning medical research in humans (“Recommendations Guiding Physicians in Biomedical Research Involving Human Subjects”, Helsinki 1964, amended Tokyo 1975, Venice 1983, and Hong Kong1989).

## Good Clinical Practice

The researchers will conduct the study following the standards of Good Clinical Practice (“Good Clinical Practice for Trials on Medicinal Products in the European Community”, CPMP Working Party on Safety of Medicinal Products, Brussels, 1990).

## Ethical procedures

The protocol and informed consent form will be presented to the Institutional Ethics Review Board (CMO) prior to the study initiation, who will have to provide a “statement of no objections”.

## Informed consent

All patients (if possible) and (if appropriate) a legally acceptable representative on the patient’s behalf and the patients caregiver will be fully informed about the study, orally and in writing. Each patient, if mentally competent, or a legally acceptable representative on the patient’s behalf, if appropriate, shall provide written consent before the patient may participate. Should the patient not be capable of providing written informed consent, written consent must be obtained from the legally acceptable representative on the patient’s behalf and verbal assent must be provided by the patient (Appendix III, IVa and IVb).

## Reporting and recording of data

Data on patients collected on clinical research forms (CRFs) in the course of this trial will be documented in a anonymous fashion (i.e. the patient will be identified only by a patient number and by patient initials). All information recorded on CRFs will be traceable back to the source documents, which are maintained in the patient’s file. The patient’s file will also indicate that he/she is participating in this clinical study.

# Randomization

Patients participating in the trial will be assigned a sequential trial number. The computer-generated list of trial numbers is linked to a randomized list with medication numbers, equivalent to 80 batches of indomethacin and 80 batches of placebo. The participating pharmacist will retain the randomization code. This procedure warrants a well-balanced initial randomization. However, a difference in the number of patients will occur when patients are withdrawn from the trial. The number of patients withdrawn from the indomethacin group will provide significant information in the final analysis of the data (“intention to treat”).

# Medication

## Medication characteristics

Indomethacin is a nonsteroidal anti-inflammatory drug (NSAID) used in the treatment of arthritis and other inflammatory disorders. It is no longer the most frequently used NSAID. However, it has the following characteristics favorable for use in Alzheimer’s disease:

- large volume of distribution
- good blood-brain barrier permeability
- results can be compared with the results from previously conducted studies

## Dosing schedule

Patients will receive indomethacin 50 mg bid. Omeprazole 20 mg will be prescribed in combination with the study medication (indomethacin or placebo), to provide gastrointestinal protection.

## Production

The amount of study medication required is 116.800 capsules of indomethacin 50 mg /placebo and 58.400 capsules of omeprazole. The generic medication will be ordered from a pharmaceutical company.

## Side effects

The risk for gastrointestinal side effects related to the use of NSAIDs in elderly people is 20 percent. In patients of 50 years and older, using a high dosage of the NSAID indomethacin and using corticosteroids at the same time, the risk of serious gastrointestinal complications can be 10 times higher, especially during the first three months. To prevent possible gastrointestinal side effects, omeprazol (20 mg once a day) will be prescribed21.

The patient’s discomfort will be small when no inconvenient side effects occur. A (small) discomfort for the patient will be the puncture in order to get blood samples.

## Concomitant medication

The patient’s concomitant medication will be maintained. Certain medication will lead to exclusion from the trial (see *5.3 exclusion criteria*).

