## Exclusion criteria

- The patient satisfies the NINDS-AIREN criteria for probable vascular dementia, including:
- presence of focal signs on neurological examination consistent with stroke
- evidence of relevant cerebrovascular disease by brain imaging (CT and/or MRI made within two years before the baseline visit)
- A known exaggerated pharmacological sensitivity or allergy to NSAID’s.
- History of peptic ulceration, gastric surgery or gastrointestinal bleeding.
- Current diagnosis of active peptic ulceration.
- Current diagnosis of severe and unstable cardiovascular disease.
- Current diagnosis of renal failure (creatinin > 200 mol/l).
- Advanced, severe and unstable disease of any type, other than Alzheimer’s disease, that may interfere with primary and secondary variable evaluations, including a medical condition which should be expected to progress, recur, or change to such an extent that it may bias the assessment of the clinical or mental status of the patient to a significant degree or put the patient at special risk.
- Intake of any of the following concomitant medications:
- salicylates
- coumarin derivatives
- ACE-inhibitors
- loopdiuretics
- Intake of any of the following concomitant medications more than two months immediately prior or during the study:
- NSAID’s
- systemic corticosteroids
- Intake of any of the following concomitant medications with a possible effect on cognition:
- estrogen
- deprenyl
- vitamin E
- neuroleptics
- anticholinergics

Patients using stable doses of cholinesterase inhibitors were eligible, with the provision that the dose should not be changed during the study. Cholinesterase inhibitors could not be initiated during the study

- Excessive use of alcohol (> 5 units/day)
- The patient is, either alone or with the aid of a caregiver, not able to reliably take the medication.

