## Measures taken in case of adverse events

An adverse event is any undesirable sign, symptom or medical condition occurring after starting the intake of the trial medication, whether considered drug-related or not. Medical conditions/diseases present before starting the trial medication are only considered adverse events if they worsened after starting the medication.

In case of an adverse event with a possible causal relationship to the use of indomethacin, the medical attendant (e.g. family physician, physician) will discontinue the trial medication. The trial ends, however the trial code will not be broken and the patient’s data will be analyzed. The medical attendant will be asked to report this decision to the investigators as soon as possible.

The medical attendant is allowed to lower the dose of the study medication, in case of a dubious causal relationship between the adverse event and the study medication. The trial code will not be broken and the patient will be considered a normal participator of the trial.

In case of a serious adverse event, the patient’s medical attendant will ask the pharmacist to announce the nature of trial medication. The code will then be broken, the medication will be discontinued and the patient’s data will not be included in the analysis of the final outcome measures. However, the data of patients discontinuing the trial will analyzed according to the “intention to treat” principle.

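### Sections 9.5 and 5.3 can remove a patient who starts a restricted drug after randomisation, while 5.4 keeps that patient; removal would weaken the ADAS-cog comparison if such starts follow decline

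*Protocol*

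**What the plan says.** Section 9.5 (Concomitant medication) has two sentences. The first is "The patient’s concomitant medication will be maintained". The second is "Certain medication will lead to exclusion from the trial", with a cross-reference to 5.3.

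Section 5.3 (Exclusion criteria) mixes entry conditions with conditions on conduct during the study:

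- NSAIDs and systemic corticosteroids come under "Intake of any of the following concomitant medications more than two months immediately prior or during the study", which covers the study period.
- Estrogen, deprenyl, vitamin E, neuroleptics and anticholinergics come under "Intake of any of the following concomitant medications with a possible effect on cognition", which has no time frame.
- On cholinesterase inhibitors it says "Patients using stable doses of cholinesterase inhibitors were eligible, with the provision that the dose should not be changed during the study" and then "Cholinesterase inhibitors could not be initiated during the study". It does not say what follows from a breach.

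Section 5.4 (Discontinuation of treatment) has one drug trigger: "Intake of systemic corticosteroids for more than two weeks". It mentions neither the cognition-active drugs nor cholinesterase inhibitors.

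Section 10.3 (Measures taken in case of adverse events) says that "the data of patients discontinuing the trial will analyzed according to the “intention to treat” principle". Appendix II schedules a check for changes in concomitant medication at baseline and at weeks 4, 8, 26, 38 and 52.

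**The concern.** Take a patient who worsens or becomes agitated around month 7 and is given a cholinesterase inhibitor or a neuroleptic by the family physician. Read through 9.5 and 5.3, this patient is out of the trial. Read through 5.4, nothing has happened that stops treatment, and the patient is assessed at week 52. Sites may differ in which section they follow.

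Over a year of progressive disease, such prescriptions are plausibly prompted by the decline that the trial measures. If so, and if indomethacin slows decline, more of them will occur on placebo. Removing these patients then takes fast decliners out of both arms, but more of them out of placebo, and the observed difference moves toward zero. An assessment that was never made at week 26 or 52 cannot be recovered by any later analysis plan, so the matter belongs in the protocol.

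**Working it through.** **1. The protocol's own figure.** Section 12.1 gives a one-year ADAS-cog change of 5.0 points, SD 7.0, a relevant difference of 3.0, one-sided 0.05 and 80% power. Per group, n = 2 × [SD × (z₀.₉₅ + z₀.₈₀) / Δ]² = 2 × [7 × (1.645 + 0.842) / 3]² ≈ 67.3. The stated 67 is reproduced. With 80 per group less 20% dropout, 64 remain, and power for 3.0 points is 0.78. That is the reference below.

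**2. Assumptions added.** The true week-52 change is taken as N(5, 7) on placebo and N(2, 7) on indomethacin. How often restricted drugs are started, how starts relate to decline, and what the drugs do to ADAS-cog are not in the protocol. All are assumed.

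**3. Removal, threshold model.** A fraction f of patients worsening by more than 12 points start a restricted drug and are removed.

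- Share above 12: placebo 1 − Φ((12 − 5)/7) = 1 − Φ(1) = 0.159; indomethacin 1 − Φ((12 − 2)/7) = 1 − Φ(1.43) = 0.077.
- For f = 1, the remaining mean is μ − 7 × φ(a)/Φ(a), with a = (12 − μ)/7. Placebo: 5 − 7 × 0.242/0.841 = 2.99. Indomethacin: 2 − 7 × 0.144/0.923 = 0.91. Difference 2.08.
- For f below 1, with p the share above 12, the remaining mean is [μ − f(μp + 7φ(a))] / (1 − fp). f = 0.5 gives 4.08 and 1.48, difference 2.60. f = 0.25 gives 4.56 and 1.74, difference 2.82.

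**4. Retention, threshold model.** If starters stay and gain s points, the difference is 3 − s × f × (0.159 − 0.077). For s = 2 to 4 this is 2.84 to 2.67 at f = 1, and 2.92 to 2.84 at f = 0.5. If the drug worsens scores, the sign of s reverses and the difference exceeds 3.

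**5. Graded model, by simulation.** The log-odds of starting rise by 0.1 or 0.3 per point of decline, with the intercept set so that about 5%, 10% or 20% of placebo patients start. Removed starters are lost in addition to the 20% dropout.

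| Starters, placebo / indomethacin | Slope | Difference if removed (power) | Kept, drug helps by 3 points | Kept, drug harms by 3 points |
|---|---|---|---|---|
| 5.0% / 3.8% | 0.1 | 2.94 (0.76) | 2.96 | 3.03 |
| 5.1% / 2.6% | 0.3 | 2.74 (0.73) | 2.92 | 3.07 |
| 10.0% / 7.7% | 0.1 | 2.89 (0.73) | 2.93 | 3.07 |
| 10.0% / 5.5% | 0.3 | 2.58 (0.70) | 2.86 | 3.13 |
| 20.1% / 15.9% | 0.1 | 2.81 (0.68) | 2.87 | 3.12 |
| 20.1% / 12.3% | 0.3 | 2.34 (0.62) | 2.76 | 3.23 |

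With slope 0 the difference stays at about 3.0 under every handling. Power after removal is then 0.76, 0.74 and 0.70 for 5%, 10% and 20% starters, so part of the power loss in the table is simply fewer patients. With starters kept, power is 0.77 to 0.78 throughout.

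**The case against.** The best defence is that 9.5 is only a pointer to the entry criteria. Section 5.3 stands under patient selection, and its cognition-active list, unlike the NSAID and corticosteroid item, does not mention the study period. For cholinesterase inhibitors it forbids initiation without naming a consequence. On that reading 5.4 does not oppose 9.5; there is only a gap. This reading is possible, but it does not fit the items in 5.3 that expressly govern conduct during the study, and 9.5 refers to 5.3 as a whole. A site could reasonably follow either reading.

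A second defence is the intention-to-treat wording in sections 8 and 10.3. It weakens any claim that excluded patients would certainly be dropped from the analysis. It does not settle the case: 10.3 concerns adverse events, its preceding sentence takes unblinded patients out of the final outcome analysis, and neither section secures week 26 and 52 assessments after a restricted drug is started.

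Three stronger conclusions that a reader might draw are not supported:

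- That the contrast shrinks whichever section is followed. If a retained drug worsens ADAS-cog, the contrast grows. If starts are unrelated to decline, or indomethacin has no effect, neither handling shifts it.
- That starts would go unrecorded. Appendix II checks for medication changes at every contact from baseline on. What is missing is a rule for what follows.
- That 5.3 should apply at entry only. This would lift its restrictions during the study, which is a clinical decision and not one for a statistical review.

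**Conclusion.** The inconsistency between 5.3, 9.5 and 5.4 is real and bears on who is assessed for the primary outcome. Removal after randomisation is the harmful route: under starts that follow decline and a working drug, the 3.0-point contrast becomes 2.94 to 2.34 in the graded model. It becomes 2.82 to 2.08 in the threshold model, where the low end requires every patient worsening by more than 12 points to start a restricted drug and be removed from the analysis. Retention moves the contrast by roughly 0.3 points or less, in a direction that depends on the drug. These are illustrations and not forecasts, since every input beyond section 12.1 is assumed. The sample size of 67 per group is not called into question on this point. The matter deserves correction because the remedy is cheap and removes an avoidable source of bias, not because a large bias has been shown.

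**What to change.** Reconcile sections 5.3, 5.4 and 9.5 so that they give one consistent account of what follows when a restricted drug is started or changed after randomisation. Which drugs are restricted during the study, and whether study drug continues after such a start, is for the sponsor to decide.

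Whatever is decided there, state in the protocol that starting or changing a restricted drug after randomisation ends neither follow-up nor inclusion in the analysis: the week 26 and week 52 assessments are still made and enter the primary intention-to-treat comparison.

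Use the medication check in Appendix II to tabulate starts by arm, and add one sensitivity analysis that treats scores after the start as missing. These two items may sit in the statistical analysis plan, and their absence from the protocol is not itself a fault.

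The cost is a few sentences and one analysis, with no new visits or data collection. The drawback is that some scores will be obtained on a newly started drug.

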# Results

## Primary outcome measure

Cognitive subscale of the Alzheimer’s Disease Assessment Scale (ADAS-cog):

The Alzheimer’s Disease Assessment Scale (ADAS) is a rating scale specifically designed for the evaluation of severity of major dysfunctions in cognitive (ADAS-cog) and noncognitive (ADAS-noncog) behaviors characteristic of persons with Alzheimer’s disease. It has become an assessment standard for use in clinical trials of new drugs being evaluated for the treatment of Alzheimer’s disease22.

The cognitive subscale of the ADAS evaluates the severity of cognitive dysfunction and consists of nine cognitive items (maximum score of 48 points) and two memory tasks (22 points), with a maximum total score of 70 points. The power calculation of this trial is based on this scale.

## Secondary outcome measures

Noncognitive subscale of the Alzheimer’s Disease Assessment Scale (ADAS-noncog): The noncognitive subscale evaluates the severity of noncognitive behavioral dysfunction. It consists of 10 items and a maximum score of 50 points.

Clinician Interview-Based Impression of Change with caregiver input (CIBIC+): The CIBIC+ is a global assessment instrument intended to provide an index of *clinically* important change that cannot be obtained from quantitative assessment measures such as mental status examinations (range 1 to 7)23.

Mini-Mental State Examination (MMSE): The MMSE is the most widely used screening instrument in Alzheimer’s disease drug studies. It is a short assessment, evaluating memory, attention, concentration, naming, repetition, comprehension, and the capacity to create a sentence. The MMSE is also frequently used to stratify patients according to disease severity. A perfect score on the MMSE is 30 and is influenced by educational achievement.

Neuropsychiatric Inventory (NPI): The NPI was developed to assess the severity and frequency of psychopathology (12 items) in dementia patients. The NPI-D assesses the amount of caregiver distress engendered by each of the neuropsychiatric disorders.24

The Interview for Deterioration in Daily living activities in Dementia (IDDD): The IDDD is a caregiver-based measure, which consists of 20 concretely worded items, reflecting the initiative to perform and actual performance of self-care and more complex activities.25

## Measures taken in case of adverse events

An adverse event is any undesirable sign, symptom or medical condition occurring after starting the intake of the trial medication, whether considered drug-related or not. Medical conditions/diseases present before starting the trial medication are only considered adverse events if they worsened after starting the medication.

In case of an adverse event with a possible causal relationship to the use of indomethacin, the medical attendant (e.g. family physician, physician) will discontinue the trial medication. The trial ends, however the trial code will not be broken and the patient’s data will be analyzed. The medical attendant will be asked to report this decision to the investigators as soon as possible.

The medical attendant is allowed to lower the dose of the study medication, in case of a dubious causal relationship between the adverse event and the study medication. The trial code will not be broken and the patient will be considered a normal participator of the trial.

In case of a serious adverse event, the patient’s medical attendant will ask the pharmacist to announce the nature of trial medication. The code will then be broken, the medication will be discontinued and the patient’s data will not be included in the analysis of the final outcome measures. However, the data of patients discontinuing the trial will analyzed according to the “intention to treat” principle.

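### Stopping medication ends the patient's trial, so ADAS-cog scores after stopping are not collected although the protocol claims intention to treat

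*Protocol*

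**What the plan says.** Section 10.3 sets out three branches.

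- **Possibly related event** ("In case of an adverse event with a possible causal relationship to the use of indomethacin"): medication is stopped and "The trial ends, however the trial code will not be broken". The patient's data are to be analysed.
- **Doubtful relationship:** the dose may be lowered, and the patient still counts as an ordinary participant. The contrast suggests that a patient who stops does not.
- **Serious adverse event:** the code is broken, medication stops and the patient's "data will not be included in the analysis of the final outcome measures". The next sentence says that patients who discontinue are analysed by intention to treat.

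Section 5.4, which concerns discontinuation of treatment, lists among its reasons "Presence of serious adverse events related to the study medication", "Questionable compliance of the patient" and "The diagnosis of Alzheimer’s disease is no longer plausible considering the course of the disease".

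Section 8 describes stoppers as withdrawn from the trial. It expects the arms to become unequal in number, regards the number withdrawn from the indomethacin group as informative, and refers to intention to treat. Section 12.1 allows for 20% dropout. Section 4 and Appendix II place the efficacy assessments at weeks 26 and 52, and nothing provides for them after medication has stopped. The only follow-up stated after an event is of the adverse event itself until it resolves (section 11.1).

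**The concern.** An intention-to-treat comparison of one-year change needs one-year outcomes on everyone randomised, including those off drug. The protocol states the principle but, in the one branch where it is explicit, ends participation when the drug stops.

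The reasons for stopping are unlikely to be neutral. Possibly drug-related events should be more frequent on indomethacin. Compliance is behaviour after randomisation. A diagnosis revised in the light of the disease course rests on information close to the ADAS-cog change itself. If leavers differ from stayers and the arms lose different proportions, the comparison of those remaining is no longer the randomised one.

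An analysis plan can choose how to handle missing scores, but it cannot recover scores that were never taken. This has to be settled in the protocol.

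**Working it through.** **1. The plan's own figure.** Inputs from section 12.1: SD 7.0, difference 3.0, one-sided alpha 0.05, power 80%.

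n per group = 2 × (1.645 + 0.842)² × 7² / 3² = 67.3, so 67 to 68 (a t-based calculation gives 68.0). The stated 67 reproduces.

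With 80 per group and 20% lost, 64 remain. SE = 7 × √(2/64) = 1.237, and power = Φ(3/1.237 − 1.645) = 78%. The allowance deals with loss of numbers only; it does nothing about who is lost.

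**2. Which scores are lost.** A patient who stops before week 26 loses both efficacy assessments. One who stops after week 26 keeps that score and loses week 52. Week 52 is therefore the main loss.

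**3. Illustration of unequal loss.** The protocol gives no dropout rate by arm and no difference between leavers and stayers, so the inputs below are assumptions. Let d be the dropout proportion in an arm and D the extra decline of leavers over stayers. The arm mean is (1 − d)m + d(m + D), where m is the stayers' mean, so m = arm mean − dD. The difference among stayers (placebo minus indomethacin) therefore shifts by (d_indomethacin − d_placebo) × D. The false-positive rate under no true effect is Φ(shift/SE − 1.645), with SE = 7 × √(1/n₁ + 1/n₂). Overall dropout is held at the protocol's 20%.

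| Dropout, indomethacin v placebo | Remaining | D | Shift (points) | One-sided false-positive rate |
|---|---|---|---|---|
| 20% v 20% | 64 v 64 | any | 0 | 0.05 |
| 25% v 15% | 60 v 68 | 2 to 7 | 0.2 to 0.7 | 0.069 to 0.14 |
| 30% v 10% | 56 v 72 | 2 to 7 | 0.4 to 1.4 | 0.093 to 0.30 |

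With D = 0 there is no shift. If leavers decline less than stayers, the shift changes sign.

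**4. Illustration for the disease-course criterion.** Suppose, again as an assumption, that the criterion removes a fraction q of patients whose one-year change is 0 or less, with change Normal(2, 7) on indomethacin and Normal(5, 7) on placebo. The proportions at or below 0 are Φ(−2/7) = 39% and Φ(−5/7) = 24%. The observed difference, truly 3.0, becomes:

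| q | Observed difference |
|---|---|
| 5% | 2.97 |
| 10% | 2.94 |
| 25% | 2.83 |
| 50% | 2.57 |

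**5. What following stoppers would do to power.** If a proportion of the indomethacin arm stops and loses all benefit, the effect over everyone randomised is 3.0 × (1 − proportion). With 80 per group, SE = 7 × √(2/80) = 1.107.

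| Stop indomethacin | Effect | Power |
|---|---|---|
| 10% | 2.7 | 79% |
| 20% | 2.4 | 70% |
| 30% | 2.1 | 60% |

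**The case against.** The strongest reply concerns scope, direction and size.

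- **Scope.** The explicit statement covers one branch only. A reader might infer that every criterion in section 5.4 is stated to end follow-up. It is not: only the patient's own withdrawal mentions leaving the study. For compliance and revised diagnosis, the end of follow-up is inferred from sections 8 and 12.1 and from the silence of Appendix II. This stands, and the point is worded accordingly.
- **Non-progressors.** A reader might infer that section 5.4 removes patients who fail to decline and so pulls the estimate towards zero. The criterion refers only to the course of the disease. An unusually fast course, or features of another dementia, would fit it equally well and would act on the other tail. The truncation model also removes patients by a final score that would not be known when they were removed. At q = 25% to 50% it takes out about 10% to 19% of indomethacin and 6% to 12% of placebo patients for this one reason, against 20% dropout for all reasons. At q = 5% to 10% the effect is negligible.
- **Differential loss.** A reader might take the sentence "The risk for gastrointestinal side effects related to the use of NSAIDs in elderly people is 20 percent" as a discontinuation rate. It is a side-effect risk; the same section prescribes omeprazole to prevent such effects, and section 9.2 gives it in both arms.
- **Dilution.** Including off-drug scores can lower power: 70% if 20% stop indomethacin and lose all benefit, against 78% with 64 completers per group. That stands as a cost. The 78%, however, assumes that completers remain comparable between arms, which is the point in doubt.

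None of this supplies the missing provision for assessment after stopping.

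**Conclusion.** The point holds in this form: explicitly for possibly related adverse events, and by implication for the other stopping reasons, the protocol does not collect efficacy outcomes after medication stops. This conflicts with its intention-to-treat claim. Section 8's own expectation that indomethacin withdrawals carry information strengthens the case.

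Neither the sign nor the size of the bias can be read from the document. The shifts of 0.2 to 1.4 points, and the truncated differences of 2.57 to 2.97, are illustrations under assumed inputs; equal dropout, or leavers no different from stayers, gives no shift. The documents do not support a claim that the result will be biased in a particular direction.

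The finding is a cheap improvement that should be made, not an error that by itself invalidates the trial.

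**What to change.** Amend sections 5.4 and 10.3 on data collection and analysis only:

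1. Separate stopping medication from leaving the study. Replace the statement that the trial ends with wording that the patient, unless consent is withdrawn, keeps the scheduled week-26 and week-52 efficacy assessments, at home if needed (section 15.2 already allows this), and that these enter the primary intention-to-treat analysis.
2. State that later doubt about compliance or diagnosis does not remove a randomised patient from assessment or analysis.
3. Reconcile the section 10.3 sentence that leaves serious-adverse-event patients out of the final outcome analysis with the intention-to-treat sentence that follows it.
4. Record the reason for stopping, so that it can be reported by arm.

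Decisions on medication and on breaking the code are not changed.

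The cost is the amendment text, up to two scheduled assessments for each patient who stops, and possible dilution of the estimated effect by off-drug scores, with the loss of power shown in step 5 of the working.
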